**Figure 1 F1:**
[figure not shown]
Flow diagram of the study.

### Surgical procedure

2.4

The patients will be operated under general anaesthesia. All surgical procedures will be done by the senior surgeon. For both methods, the patient is set in a beach chair position on a light transmitting table with standard armrests.

The traditional deltopectoral approach will be used in patients of locking plate group. Correct repair of the fracture site is performed under C-arm fluoroscopy, and then temporary Kirschner wire or reduction forceps is used to fix the fracture fragments. Locking plate is placed along the lateral edge of biceps groove at the proximal humerus. To prevent subacromial impact, the plate is placed 5 to 8 mm below the tip of the greater tubercle and 2 to 4 mm outside the biceps groove. The correct position of the plates and screws is identified by anteroposterior and axillary fluoroscopy.

The anterolateral approach will be used in patients of intramedullary nail group. A 4-cm-long incision will be made lateral to the acromion parallel to the Langer line. The insertion point was situated at the top of the humeral head, medial to the major tubercle, and lateral to the internodular sulcus. A Proximal Humeral Nail will be inserted without reaming after the fracture is fully reduced. The distal and proximal screws are implanted with assistance. Then the rotator cuff is restored, and the incision is sutured the absence of vacuum drainage.

### Rehabilitation protocol

2.5

Two groups will use the same postoperative rehabilitation protocol. The outpatient physiotherapy program is arranged at 3 intervals, 10 times each time, lasting for 25 minutes a day. With the help of physiotherapists, passive protected area exercises begin on the first day after surgery. The limb was protected with sling for 4 weeks. Four to six weeks after the operation, they begin comprehensive active and active auxiliary exercise training. Intensive training began 3 months after operation. The patients are followed up at 2 weeks, 6 weeks, 12 weeks and every three months thereafter. The fracture healing and the cervical trunk angle are evaluated by radiology.

### Postoperative outcome evaluation

2.6

Clinical outcomes include Intraoperative blood loss, operation time, Constant-Murley score (CMS), Disability, Arm, Shoulder and Hand (DASH) score, shoulder range of motion (such as external rotation), and postoperative complications. CMS is a multiple item functional scale used to assess pain, daily activities, range of motion, and shoulder strength. The range of the score is 0–100, indicating the worst and best shoulder function. DASH score is sensitive, reliable and effective in fracture patients, which is broadly applied to evaluate the postoperative outcomes of these patients. It consists of 30 questions, converted into one of 100 points. A higher score indicates greater disability. Image results will be obtained on two planes, and postoperative implant location, secondary humeral head displacement, osteonecrosis, nodule absorption, and secondary fixation failure will be evaluated. Implant malposition refers to the suboptimal implant position in postoperative imaging, without mechanical influences for shoulder function. Secondary fixation failure refers to severe loss of reduction during follow-up.

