### Statistical analysis and sample size calculation

2.7

Continuous data are expressed as mean and standard deviation, and classified data are expressed as absolute numbers and percentages. Student *t* test was used for continuous variables in normal distribution, and Mann Whitney *U* test was used for non-normal distribution. Categoric variables were dealt applying the χ^2^ test or Fisher exact test. The total number of complications was dealt considering the number of possible circumstances. The significance level was defaulted as *P* < .05.

The sample size was calculated based on an average difference of 10% between groups with constant Murley scores adjusted for age and gender. The standard deviation was 10 points, α was 5%, and the power was 80%. The sample size of 25 patients was required for each study group. To compensate for potential withdrawal during the follow-up period, each group included at least 32 patients.

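### The Constant-Murley score sizes the trial, but no outcome is named primary and no visit is chosen, so the 5% error rate and 80% power belong to no defined comparison

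*Protocol article*

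**What the plan says.** - **Outcomes (section 2.6).** "Clinical outcomes include Intraoperative blood loss, operation time, Constant-Murley score (CMS), Disability, Arm, Shoulder and Hand (DASH) score", with range of motion and postoperative complications, make six clinical outcomes, none ranked above another. Range of motion is given only by example. The same section adds five imaging items: "postoperative implant location, secondary humeral head displacement, osteonecrosis, nodule absorption, and secondary fixation failure will be evaluated".
- **Visits (section 2.5).** "The patients are followed up at 2 weeks, 6 weeks, 12 weeks and every three months thereafter". No final visit is given, and no visit is singled out for comparing the groups.
- **Tests (section 2.7).** "Student *t* test was used for continuous variables in normal distribution, and Mann Whitney *U* test was used for non-normal distribution". Categorical data get a chi-square or Fisher test. For the threshold: "The significance level was defaulted as *P* < .05". One sentence on the total count of complications is unclear, and it sets no error control across outcomes or visits.
- **Sample size (section 2.7).** It rests on a 10% difference in Constant-Murley score with SD 10 points, α 5% and power 80%. The result is 25 per group, raised to at least 32 for withdrawals. No time point is attached.
- **Aim (Introduction and Discussion).** Functional, complication and imaging results are to be compared, with no order of importance. The abstract expects the trial to inform which technique is better, without saying which result decides this.

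**The concern.** An alpha of 5% and a power of 80% are properties of one test, on one outcome, at one time. The article gives both figures but does not identify that test. Constant-Murley is the only candidate with a planned difference behind it, and even that has no visit.

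Two choices are therefore open when the data arrive: which outcome carries the conclusion, and at which visit. If either is made after results are seen, the real chance of a false claim exceeds 5% and a reader cannot tell by how much. The power statement suffers too. Shoulder function can be expected to change during recovery, so a 10% difference read as a share of the mean is a different number of points at different visits.

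**Working it through.** **Inputs from the article:** SD 10 points, α 0.05, power 0.80, 25 per group (32 with the withdrawal allowance), six clinical outcomes, visits at 2, 6 and 12 weeks and then three-monthly.

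**Assumptions:** two-sided tests (sidedness is not stated), a 12-month horizon, and all correlations below.

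**Step 1: the plan's own figure.** For two means, n per group = 2 × SD² × (1.960 + 0.842)² / difference².

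- If 10% means 10 points: 2 × 100 × 7.849 / 100 = 15.7, so 16 per group, which is not 25.
- If 10% means a tenth of an assumed reference mean of 80, the difference is 8 points: 2 × 100 × 7.849 / 64 = 24.5, so 25 per group. This matches.
- Withdrawals: 25 / (1 − 0.20) = 31.25, so 32. This also matches, with 20% loss assumed.

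The stated 25 thus fits a single two-sided Constant-Murley comparison if the reference mean is about 80. The article does not give that mean or the visit it would belong to.

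**Step 2: free choice of outcome, each of the six tested once.** If independent, the chance of at least one false positive is 1 − 0.95⁶ = 1 − 0.735 = 26.5%. With equal correlation r between the test statistics (simulated multivariate normal, at least 200,000 draws):

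| r | at least one P < .05 |
|---|---|
| 0.3 | 24% |
| 0.5 | 21% |
| 0.7 | 16% to 17% |
| 0.9 | 11% |

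The rate falls to about twice 5% only when all six correlate near 0.9. That is implausible for a mix of blood loss, operation time, function and complications.

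**Step 3: Constant-Murley accepted as the lead, with free choice of visit.** To 12 months the schedule gives six visits: 2, 6 and 12 weeks, then about 6, 9 and 12 months.

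| Correlation between visits | r = 0.8 | r = 0.5 |
|---|---|---|
| Same for every pair of visits | 14% | 21% |
| r between neighbouring visits, decaying with distance | 17% | 24% |

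The range is 14% to 24%.

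**Step 4: one outcome at one visit.** The error rate for the main claim is 5%, as section 2.7 states.

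**The case against.** The strongest reply is that Constant-Murley is the lead outcome in all but name, since it alone has a planned difference, SD, alpha and power. This stands in part: it makes Constant-Murley the natural choice. It does not supply the visit, and step 3 shows that the visit alone matters.

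A second reply is that this is a condensed article and an analysis plan may exist. That is right for multiplicity procedures such as a Holm correction, whose absence is no defect here. The primary outcome and its time point are different, because they define the trial's question. The article has an outcome section, a visit schedule and a sample-size section, and together these leave both open.

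Several stronger readings are tempting, and the text does not support them:

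- **Every outcome is tested at every visit.** The article does not say so. The schedule sits in the rehabilitation section, and blood loss and operation time are measured only once.
- **Groups are compared at a last visit after unequal follow-up.** The missing end of follow-up would allow this, but no such analysis is described.
- **A win on any outcome decides the trial.** This rule is not written. The familywise rates in step 2 apply only if someone adopts it.
- **All eleven items count equally, giving 1 − 0.95¹¹ = 43%.** This overstates the risk. The imaging items are mostly events, for which the article allows "Fisher exact test". With 32 per group, that test's true size is about 0.2%, 1.1% and 1.9% at assumed event rates of 5%, 10% and 15%. The same conservatism applied to complications lowers the six-outcome range only slightly, to about 15% to 22%. A chi-square test would be less conservative.

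**Conclusion.** The point holds in this form: the article states an error rate and a power but does not define the comparison they describe. Constant-Murley is implied, never named as primary, and has no visit.

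Leaving the choice of outcome or the choice of visit open could each raise the false-positive rate to roughly three to five times 5%: about 17% to 24% for six outcomes tested once, and about 14% to 24% for Constant-Murley over six visits. These figures show what the open choices could cost. They are not the error rate of a procedure the article lays down. They rest on two-sided tests of exact 5% size, the correlations shown and, for the visit figure, a 12-month horizon.

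**What to change.** Before any outcome data are seen:

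1. Name the Constant-Murley score at one scheduled visit common to all patients as the single primary outcome, tested at two-sided 5%. Twelve months is one example and already falls within the three-monthly schedule.
2. State a common end of follow-up.
3. Label all other outcomes and visits secondary, report them with estimates and 95% confidence intervals, and say that they will not decide which technique is better.

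This takes two or three sentences and leaves the sample size as it is, because Constant-Murley already sizes the trial. The cost is that secondary results no longer support a confirmatory claim at nominal P < .05. The timing matters: a primary outcome or visit chosen after the results are known would not restore the 5% error rate.

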### Statistical analysis and sample size calculation

2.7

Continuous data are expressed as mean and standard deviation, and classified data are expressed as absolute numbers and percentages. Student *t* test was used for continuous variables in normal distribution, and Mann Whitney *U* test was used for non-normal distribution. Categoric variables were dealt applying the χ^2^ test or Fisher exact test. The total number of complications was dealt considering the number of possible circumstances. The significance level was defaulted as *P* < .05.

The sample size was calculated based on an average difference of 10% between groups with constant Murley scores adjusted for age and gender. The standard deviation was 10 points, α was 5%, and the power was 80%. The sample size of 25 patients was required for each study group. To compensate for potential withdrawal during the follow-up period, each group included at least 32 patients.

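### The trial is sized on Constant-Murley scores adjusted for age and gender, but the plan defines only the 0–100 score and names only unadjusted two-group tests

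*Protocol article*

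**What the plan says.** Section 2.7 (Statistical analysis and sample size calculation) gives the planning assumptions:

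- The target is an "average difference of 10% between groups with constant Murley scores adjusted for age and gender".
- On spread: "The standard deviation was 10 points".
- On error rates: "α was 5%, and the power was 80"%.
- The result: "The sample size of 25 patients was required for each study group", raised to at least 32 per group for withdrawals.

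For the analysis of continuous outcomes, the same section says that a Student t "test was used for continuous variables in normal distribution, and Mann Whitney" U applies when the distribution is not normal. Neither test takes covariates, and the section names no adjusted model.

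Section 2.6 (Postoperative outcome evaluation) describes the Constant-Murley score thus: "The range of the score is 0–100, indicating the worst and best shoulder function". It defines no version of the score adjusted or normalised for age and gender.

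**The concern.** The quantity used for planning and the quantity set for analysis are described differently. The phrase "constant Murley scores adjusted for age and gender" has two natural readings, and neither fits the rest of the text.

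- **Covariate adjustment.** The planned comparison is then a mean difference holding age and gender fixed. Section 2.7 provides only unadjusted tests. Randomisation balances age and gender on average, so such a test is still valid, but it leaves in the error term any variation that age and gender explain.
- **A normalised score.** The outcome is then the score expressed relative to an age and gender reference. A two-group test on that score would match the sizing, but section 2.6 describes only the 0–100 score.

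The target is an average difference, yet the rule replaces the mean comparison with a rank comparison when the data look non-normal. For the score on which the trial was sized, the tested quantity then depends on the observed distribution.

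At stake are power and a clear definition of the main functional result. If nothing is settled before the data are seen, unadjusted, adjusted, normalised and rank results would all be open to choice.

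**Working it through.** **Inputs from section 2.7:** SD 10 points, α 5% (two-sided assumed), power 80%, 25 per group, difference 10% with no reference value given.

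**Assumptions, not in the document:** the difference in points (10, or 8 as 10% of a mean of 80), and R², the share of score variance explained by the covariates (0.05 to 0.30).

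**Step 1. The plan's own figure.** n per group = 2 × (1.960 + 0.842)² × SD² / Δ² = 2 × 7.849 × 100 / Δ².

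- Δ = 10 points: 1569.8 / 100 = 15.7, so 16 (17 with the t distribution). This does not give 25.
- Δ = 8 points: 1569.8 / 64 = 24.5, so 25 (26 with the t distribution). This matches.

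The 8-point reading is used below because it matches 25, with 10 points alongside.

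**Step 2. Reference power.** Two-sample t test (noncentral t), 25 per group, SD 10: 79% for 8 points and 93% for 10 points.

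**Step 3. If SD 10 is the raw SD.** Adjustment shrinks the SD to 10 × √(1 − R²). The small loss of degrees of freedom for the covariates is ignored.

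| R² | Residual SD | Adjusted power, 8 points |
|---|---|---|
| 0.05 | 9.75 | 81% |
| 0.10 | 9.49 | 83% |
| 0.20 | 8.94 | 87% |
| 0.30 | 8.37 | 91% |

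**Step 4. If SD 10 is the adjusted SD.** The unadjusted test faces a raw SD of 10 / √(1 − R²).

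| R² | Raw SD | Unadjusted power, 8 points | Unadjusted power, 10 points |
|---|---|---|---|
| 0.05 | 10.26 | 77% | 92% |
| 0.10 | 10.54 | 75% | 91% |
| 0.20 | 11.18 | 70% | 87% |
| 0.30 | 11.95 | 64% | 83% |

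If all 32 per group completed, the 8-point column would run from 87% (R² 0.05) to 75% (R² 0.30).

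**Step 5. If a normalised score was meant.** No power calculation separates plan from analysis, because a two-group test on that score is the planned comparison. The defect is then only that section 2.6 does not define that score.

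**The case against.** The strongest reply is that the adjustment wording directly follows the name of the score and may describe the score itself. A target in percent fits a normalised score, and the stated tests would then match the sizing. This stands as a possible reading, and it is why the document cannot be said to test the raw score: it never says so. It does not clear the plan, because section 2.6 would then describe a different score.

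Second, a material power loss needs several assumptions together: covariate adjustment, SD 10 being the residual SD, a target near 8 points, and R² of about 0.2 or more. This also stands. If SD 10 is the raw SD, the unadjusted test loses nothing against the plan and only forgoes a gain. The sizing sentence names age and gender only, so in Step 4 R² should be read as their share alone. In Step 3 it may also include fracture type.

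Third, a reader might infer that the unadjusted analysis is biased. It is not: under randomisation the two-group test is valid.

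Fourth, a reader might infer that the tests discard the earlier scores of patients who withdraw, and that a repeated-measures model is needed. The document does not support this. It names no analysis visit and does not say that the Constant-Murley score is taken at every follow-up visit.

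Fifth, a rank test does not hide the mean difference entirely, since section 2.7 reports continuous data as mean and standard deviation. That is fair, but the p-value would still belong to a different quantity from the one used for sizing.

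An unseen analysis plan could supply model details. The mismatch, however, lies between statements this document itself makes.

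**Conclusion.** The point holds as one of consistency and efficiency, and it should be corrected before data are seen. It is not a flaw that invalidates the trial. The sizing refers to an age- and gender-adjusted score, while the tests are unadjusted and the defined outcome is the 0–100 score.

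The size is conditional. At 25 per arm, with an assumed 8-point difference and an assumed R² of 0.05 to 0.30, adjustment adds about 2 to 12 percentage points of power if SD 10 is raw. If SD 10 is the adjusted SD, the unadjusted test falls about 2 to 15 points short of the 79% reference. At the lower end of R² the effect is small. With a 10-point difference, unadjusted power stays above 80% throughout. The missing reference for the 10% is a separate matter and moves the sample size more (25 against 16 or 17).

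**What to change.** 1. In sections 2.6 and 2.7, state whether the 0–100 score or an age- and gender-normalised score is analysed, and on which scale the 10% difference and the SD of 10 apply. If the normalised score was meant, define it in section 2.6.
2. Make the main Constant-Murley analysis a linear model with treatment, age, gender and fracture type (three-part or four-part). Report the adjusted mean difference with its 95% confidence interval whatever the distribution looks like.
3. Keep Mann-Whitney as a sensitivity analysis, and use the same form for DASH.

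The cost is a few sentences and little programming. No new data are needed: age and fracture type are needed for eligibility, and gender is already part of the planning assumption. The sample size need not change on account of this point.

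### Total complications appear to be counted against possible events rather than patients; if tested that way, the P value is too small whenever complications cluster within a shoulder

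*Protocol article*

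**What the plan says.** Section 2.7 of the protocol article first sets the general rule for categorical data: "Categoric variables were dealt applying the χ^2^ test or Fisher exact test". The next sentence treats complications separately: "The total number of complications was dealt considering the number of possible circumstances". The threshold follows: "The significance level was defaulted as *P* < .05". Nothing in the section says whether a complication total is divided by patients or by possible occurrences. It also does not say which test, if any, is applied to the total, or how a patient with several complications is counted.

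Section 2.6 names postoperative complications among the clinical outcomes. It then lists imaging assessments made on the same shoulder: "postoperative implant location, secondary humeral head displacement, osteonecrosis, nodule absorption, and secondary fixation failure will be evaluated". One of these is defined in terms close to another: "Secondary fixation failure refers to severe loss of reduction during follow-up".

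Section 2.3 allocates patients to nail or plate. The Introduction and the Discussion both give complications as one of three things to be compared, beside functional outcomes and imaging.

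**The concern.** The sentence takes the total number of complications out of the ordinary rule for categorical variables and ties it to a number of possible occurrences. Read plainly, a group with n patients and K types of complication would have a denominator of n × K.

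Chi-square and Fisher tests need independent observations. Several events in one shoulder, after one operation on one fracture, are not obviously independent. Here two listed events can describe the same process: a displaced head may also be a severe loss of reduction, and no rule in the article prevents one event from being scored under both. If events cluster, a few patients with several problems each can produce a nominally significant difference between implants that a count of affected patients would not show. Complications are a stated aim of the trial, so such a result would carry weight.

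**Working it through.** The article gives no figure for the complication comparison, so there is no printed result to reproduce. The check asks what error rate an event-level test would have when the implants do not differ.

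**Inputs from the article**
- At least 32 patients per group (section 2.7; 25 before the allowance for withdrawal).
- Significance level 0.05 (section 2.7). Two-sided is assumed, as the article does not say.

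**Inputs assumed, because the article does not give them**
- Number of event types K: 5, the count of the imaging items in section 2.6, and 3 as a smaller alternative.
- Probability of each event type: 0.05 to 0.15.
- Within-patient correlation (ICC): 0 to 0.3.

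**Step 1: nominal denominator.** With K = 5, 32 × 5 = 160 possible events per arm. With K = 3, 32 × 3 = 96.

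**Step 2: design effect.** The variance of the event total is inflated by DE = 1 + (K − 1) × ICC. A chi-square test that ignores this has a true two-sided error of 2 × [1 − Φ(1.96 / √DE)].

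| ICC | DE, K = 3 | Error, K = 3 | DE, K = 5 | Error, K = 5 |
|---|---|---|---|---|
| 0 | 1.0 | 5.0% | 1.0 | 5.0% |
| 0.1 | 1.2 | 7.4% | 1.4 | 9.8% |
| 0.2 | 1.4 | 9.8% | 1.8 | 14.4% |
| 0.3 | 1.6 | 12.1% | 2.2 | 18.6% |

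**Step 3: simulation.** Beta-binomial data with no true difference and 32 patients per arm agree with the formula.
- K = 5, event-level chi-square: about 5% at ICC 0, then 9-10%, 14-15% and 18-19% at ICC 0.1, 0.2 and 0.3.
- K = 3, event-level chi-square: about 6-7%, 9-10% and 11-12% at the same three correlations.
- K = 5, event-level Fisher: about 3-4% at ICC 0, 5-8% at 0.1, 10-12% at 0.2 and 13-15% at 0.3. Fisher is conservative to begin with, so it inflates less, but it still passes 5% once correlation is moderate.

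**Step 4: the same data with one unit per patient.** Testing any complication (yes or no) in 32 versus 32 patients gave an error of 5.0-6.2% with chi-square and 1.2-3.5% with Fisher, at every correlation tried (up to 0.5).

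**Step 5: an invented illustration.** Suppose 20 complications in one arm and 9 in the other, with K = 5.
- By event: the pooled proportion is 29/320 = 0.0906 and the difference is 11/160 = 0.0688. The standard error is √(0.0906 × 0.9094 × 2/160) = 0.0321, so z = 2.14 and P = 0.032 (Fisher 0.0499).
- By patient, if these arose in 10 and 6 of 32 patients: the pooled proportion is 16/64 = 0.25 and the difference is 4/32 = 0.125. The standard error is √(0.25 × 0.75 × 2/32) = 0.108, so z = 1.15 and P = 0.25 (Fisher 0.39).

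**The case against.** A reader might infer that the plan definitely commits to an event-level chi-square test, that its P value is always too small, and that the sample is inflated fivefold. The article does not support that.

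- **Denominator and test.** The sentence names neither. The English is loose throughout, and the phrase could mean a descriptive total, or each complication reported against the patients at risk of it. The link to chi-square or Fisher comes from the adjacent sentence and is not stated.
- **Five event types.** That count comes from the imaging list in section 2.6. The aims list complications and imaging separately, and no passage says that these five items make up the complication total. Any fivefold figure is therefore an assumption.
- **Clustering.** At zero correlation the event-level test holds its level. The article gives no correlation and no complication rate. If overlapping events were coded as mutually exclusive, correlation would be pushed the other way.
- **Importance.** The sample size is built on the Constant-Murley score, and no power is claimed for complications. Detailed counting rules may be in a full protocol or analysis plan that is not shown.

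All of this limits the strength of the point, but it does not remove it. The article does publish a rule for the complication total, so this is more than an omitted detail. An event denominator remains the most natural reading of that rule. Under any other reading, the sentence still fails to tell an analyst what to divide by.

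**Conclusion.** The point holds in conditional form and should be fixed. As worded, the rule most naturally points to possible events as the denominator. If a chi-square or Fisher test is applied to that total, it ignores that the patient is the randomised unit, and it gives too small a P value whenever complications cluster. The overlapping definitions in section 2.6 make positive clustering the likelier case, but they do not prove it.

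The size can only be given as a range: for chi-square, a modest excess over 5% with three event types and weak correlation, up to nearly four times nominal with five types and a correlation of 0.3. This rests on the assumed number of types, event rates and correlations. The direction of the error depends only on correlation being positive. The Constant-Murley comparison is not affected.

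**What to change.** Replace the sentence in section 2.7 with wording such as: *The groups will be compared on the number of patients with at least one complication, by chi-square or Fisher exact test, with the patients in each group as the denominator. Each type of complication will also be reported by number of patients. Total numbers of complications will be given descriptively, or analysed only by a method that keeps the patient as the unit.*

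A particular count model, a permutation test, or a rule for coding a loss of reduction that fits two categories would be optional additions. The defect is cured without them.

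The change affects analysis wording only and needs no further patients or data. Its downside is that the P value for complications will probably be larger and less favourable, and that a yes/no outcome per patient does not distinguish one complication from several. The wording should be settled before outcome data are seen, so that the denominator is not chosen in the light of the results.
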